## Abstract

**Background:**

The demands of daily life often cause mothers high levels of distress and other negative emotions. Anger, including harsh verbal discipline, has been linked to child maltreatment, with long-term adverse effects on a child’s well-being. It is critically important to teach mothers stress management and emotion regulation in addition to parenting skills, but this is yet to be conducted in a formalized manner. Strengthening the multiple protective factors that constitute resilience helps reduce distress. The aim of this study is to evaluate the efficacy of a resilience-enhancement program for mothers.

**Methods:**

We designed a two-arm, parallel, randomized trial with an active control. Mothers and their partners with children between three and six years old will be recruited. Following an online baseline survey, 140 mothers will be randomly allocated to either an intervention or control group. Self-report assessment will be conducted online post-intervention and at a two-month follow-up. The control group will participate in a serious of group discussions. The intervention group will participate in four bi-weekly 120-min sessions of a Cognitive Behavior Therapy-based program designed to enhance resilience, focusing on emotion regulation through cognitive reappraisal. Participants will be encouraged to apply and share the skills they acquire with their partner and children at home. Partners will also be assessed to explore their indirect influence from the mothers. Intention-to-treat analysis will be conducted and the two groups will be compared, applying covariate analysis. The primary outcome of the intervention is improved resilience. Secondary outcomes include improved anger control, self-esteem, cognition of children’s misbehavior, and reduced parental stress.

**Discussion:**

To the best of our knowledge, this study will evaluate the first resilience-enhancement program focused on emotion regulation for mothers in Japan. It will contribute to the existing body of knowledge on building emotional resilience. If the program is found to be effective, it will provide an alternative means to enhance mothers’ resilience against stress and improve their ability to regulate emotion. In so doing, it will offer a way to prevent child maltreatment and protect the mental health of children and families.

**Trial registration:**

UMIN000027232, May 3, 2017.

## Background

Parents experiencing high levels of stress have been found to show a greater frequency of controlling and abusive parenting behaviors [1–3]. Japanese people generally tend to suppress negative emotions, especially anger, towards others [4]; however, when it comes to the expression of anger towards their children, the situation can be quite different. The most frequently reported parental stress response emotion among Japanese mothers with children older than 18 months is anger and irritation, more often than anxiety and depression [5, 6]. Among Japanese mothers of three-year-olds, 62.2% had angry outbursts toward their children in times of stress; of these, 86.7% had resorted to harsh verbal discipline [7].

Harsh verbal discipline has long-term, adverse effects on children’s well-being [8]. Exposure to parents’ verbal aggression during childhood increases the risk for the development of psychopathological issues and is associated with alterations in brain structure [9, 10]. Parents’ harsh verbal discipline has been associated with adolescent conduct problems and depressive symptoms; maternal and paternal warmth did not moderate their longitudinal associations [11]. There is, therefore, an urgent need to support parents in decreasing parental stress and, consequently, child maltreatment.

Japan’s Ministry of Health, Labor and Welfare has recently recognized that the widespread use of verbal aggression and physical punishment against children is a serious concern and launched a public campaign that encourages parents to regulate their emotions and in understanding their children’s developmental stages. However, there is little practical support available to parents to help them understand and implement these suggestions. Appropriate parenting skills training is not enough to prevent maltreatment, and an intervention that decreases stress and increase emotion regulation in combination with parenting skills training might be more effective [6, 12]. As parenting involves multi-faceted stressors, one of the key components of this approach is the enhancement of resilience against stress [13].

In the field of psychology, resilience refers to the “process of effectively negotiating, adapting to, or managing significant courses of stress or trauma” [14]. For many individuals of all ages, resilience is a normative recovery process that occurs in response to stressors. Early resilience research was mostly focused on children [15, 16] and emerged from the investigation of good adaptation and healthy development among children who had experienced adverse life events [17]. Resilience research has been expanding to include larger population groups with specific needs and difficulties, and parental resilience has been identified as a research priority that has been largely neglected [18–20]. Along with resilience against serious traumatic events, the everyday stress of parenting is another area of importance [21, 22].

Studies have shown that resilience positively correlates with lower psychological distress and greater well-being [20], and one of the benefits of applying the resilience framework to a parenting intervention is its emphasis on primary prevention, rather than targeting serious, pre-existing maladjustment [23, 24]. Parental self-efficacy fosters a sense of empowerment and promotes an adaptation process that leads to good-quality parenting [25]. Evidence also suggests that proactive parenting can enhance children’s resilience, increasing their self-confidence [26].

Another benefit of the resilience-enhancement approach is that people are more receptive and willing to participate in programs that support them in developing new skills and emphasize their strengths [27]. With this approach, mother’ strengths can be harnessed to improve their children’s future welfare and to learn from and let go of regrets over their past inappropriate parenting; this has been shown to be effective in driving positive changes [20]. Through the application of this approach, individuals can learn about and strengthen their resilience [16], which ultimately empowers them to change. Since resilience is a multifaceted concept, enhancement requires strengthening multiple protective factors relevant to the target population [20, 28] such as emotion regulation, self-esteem, coping skills, effective problem solving, and family and peer relationships [29, 30].

Emotion regulation (ER) has been suggested as an important factor of resilience [31]. ER refers to “extrinsic and intrinsic processes responsible for monitoring, evaluating, and modifying emotional reactions, their intensive and temporal features in particular, to accomplish one’s goals” [32, 33]. While stressful events often lead to emotional reactions, it is not the event itself that causes a particular emotion, but rather the person’s cognitive appraisal of the event. Cognitive reappraisal (CR) involves reframing an emotionally negative situation in a more positive way to decrease the experience of negative emotion [31, 34]. CR and resilience are positively related, while emotional suppression relates negatively to well-being [35–38].

Multiple stressors experienced by mothers including children’s misbehavior, lack of their partners’ support, and low self-esteem or self-image may impair their resilience. Mothers who hold their children to irrational demands might be prone to anger and the application of harsh disciplinary practices. In order to enhance resilience, parents also need to maintain a positive self-image, accepting their own weaknesses and imperfections [39, 40]. The implementation of CR principles by mothers should improve their resilience and may also decrease their anger and anger expression.

In a randomized controlled trial that evaluated the effectiveness of the resilience-enhancement intervention among university students, the intervention group received four weekly, two-hour sessions to learn the skills necessary to change cognitions related to stressful events. The result showed higher resilience, more effective coping strategies, and higher scores on most of the protective factors targeted [30].

In the first systematic review and meta-analysis of resilience-enhancement programs in adults, the body of randomized trial evidence showed a modest but consistent benefit of these programs in improving a number of outcomes, including resilience, quality of life, self-efficacy, depression, and stress [41].

To the best of our knowledge, no studies have used a randomized controlled trial to evaluate a resilience-enhancement program targeting mothers with a focus on emotion regulation.

### Aim

The aim of this study is to assess the efficacy of a resilience-enhancement program for mothers focused on emotion regulation using a randomized controlled trial.

## Methods/design

This is a non-blinded study with two parallel arms and an active control group (see Fig. 1). The allocation ratio of both groups is 1 to 1.

**Fig. 1 Fig1:**
[figure not shown]
Overview of protocol

### Participants

Participants will be recruited at kindergartens, nursery schools, and other facilities where children and their parents gather, in two prefectures in Japan. Recruitment material in the form of flyers and posters will be held to the following criteria:

#### Inclusion criteria

Mothers and their partners who have at least one child between three and six years.

#### Exclusion criteria

Those who are diagnosed with a mental disorderThose who do not speak or read Japanese

### Sample size calculation

Sample size was calculated using a statistical power analysis. To detect an effect size of d = 0.62 between the two conditions, with α = .05 (two-tailed) and β = 0.8, 64 dyads in each group are needed. Considering attrition possibility and feasibility, 140 mothers and their partners will be recruited.

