### Statistical analysis

Data will be analyzed according to the intention-to-treat principle. The primary and secondary outcome measures will be analyzed at post-intervention and two-month follow-up using analysis of covariance to adjust for baseline differences between the groups. Subgroup analysis will be conducted using stratification factors including mother’s age, the area they live in, and number of children.

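### The stated 64 per group does not follow from d = 0.62 at 80% power, which needs 42; 64 is the requirement for d = 0.50, and β is printed where power is meant

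*Protocol article*

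**What the plan says.** The Sample size calculation section of the Protocol article gives the effect size, significance level, β and resulting number in one sentence: "d = 0.62 between the two conditions, with α = .05 (two-tailed) and β = 0.8, 64 dyads in each group are needed". The next sentence moves to the recruitment target: "Considering attrition possibility and feasibility, 140 mothers and their partners will be recruited". Methods/design fixes equal groups: "The allocation ratio of both groups is 1 to 1". The Statistical analysis section plans the comparison "using analysis of covariance to adjust for baseline differences between the groups".

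The article gives no attrition rate, intraclass correlation, design effect, multiplicity correction or baseline correlation as an input to the calculation.

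**The concern.** A standardised effect, a two-sided significance level and a power determine the group size for a comparison of two means. The article prints all three with a result and says that the result follows, so the claim can be checked directly. The result looked too large for an effect of 0.62 and familiar as the answer for 0.50. Separately, a β of 0.8 taken at face value means 20% power, which no one plans for.

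What is at stake is the only justification given for the trial's size. As printed, a reader cannot tell whether the trial was designed to detect 0.62 with a wide margin or 0.50 at the conventional 80%, or whether an allowance was made and not reported.

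**Working it through.** **Inputs.** From Sample size calculation: d = 0.62 (standardised, so SD = 1), two-sided α = 0.05, β printed as 0.8, and 64 per group. From Methods/design: 1:1 allocation.

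**Formula.** Under the normal approximation, n per group = 2(z₁₋α/₂ + z_power)² / d². The exact version uses the noncentral t distribution with noncentrality d√(n/2), and runs about one participant per group higher here.

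**Attempt to reproduce 64 from the stated inputs, reading β = 0.8 as power 0.80.**
- Normal approximation: 2(1.960 + 0.842)² / 0.62² = 15.70 / 0.3844 = 40.8, so 41.
- Noncentral t: 41.8, so 42 per group (84 in total).

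This is not 64.

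**β = 0.8 read literally (power 0.20).** Noncentral t gives 7.5, so 8 per group.

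**Other settings.**

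| d | Two-sided α | Power | n per group (noncentral t) |
|---|---|---|---|
| 0.62 | 0.05 | 0.80 | 42 |
| 0.62 | 0.05 | 0.90 | 56 |
| 0.62 | 0.05 | 0.95 | 69 |
| 0.62 | 0.01 | 0.80 | 63 |
| 0.50 | 0.05 | 0.80 | 64 (63.8) |

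A one-sided 5% test at d = 0.62 and 80% power gives 33. The only setting tried that returns 64 is d = 0.50 with two-sided α = 0.05 and 80% power. The nearest miss at d = 0.62 (α = 0.01, giving 63) contradicts the printed α.

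**Could an adjustment bridge 42 to 64?**
- Attrition: it would have to be 1 − 42/64 = 34%. The article adds its attrition allowance after the 64, going from 2 × 64 = 128 to 140.
- Design effect: 64/42 = 1.52 would be needed. With 1 + (m − 1) × ICC, that corresponds to an ICC near 0.06 for session groups of m = 10, or near 0.10 for m = 6. Both ICCs are illustrative assumptions; the article states none.
- Baseline adjustment by analysis of covariance: this lowers the required number, so it moves away from 64.

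**What the planned numbers deliver (noncentral t, two-sided 5%).**

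| n per group | Power at d = 0.62 | Power at d = 0.50 |
|---|---|---|
| 64 | 93.6% | 80.1% |
| 70 (all 140 analysed) | 95.4% | 83.6% |

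The smallest effect detectable with 80% power at 64 per group is d = 0.50 (0.499).

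**The case against.** The strongest reply is that nothing in the trial's conduct depends on the discrepancy. Under either candidate effect size, 64 per group reaches at least 80% power by this simple calculation, and no enrolment figure, outcome or analysis would change. The β is an evident slip of label. An effect of 0.62 is specific enough that it may have a source, and a clustering allowance of about 1.52 may have been applied and left out of the article.

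Much of this stands. The error is conservative, and the literal 20% power reading deserves no weight beyond correcting the label. But an allowance that may have been used does not make the printed sentence true: it says that 64 follows from the inputs shown, and it does not. This is also not detail left to a fuller document, because the article itself prints both the inputs and the result.

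A reader might infer more than the documents support:
- **That the trial is underpowered.** It is not, on its own calculation, at either 0.62 or 0.50.
- **That d = 0.50 was the intended target.** The exact match is suggestive, but the documents do not show which figure is wrong.
- **That 0.50 is the better planning value because earlier programs "showed a modest but consistent benefit of these programs" and the comparator here is active.** The Background attaches no number to that benefit, so it cannot separate 0.50 from 0.62. The same section also cites a student trial of a similar four-session format that found higher resilience.
- **That the step from 128 to 140 allows too little attrition.** The article gives no expected rate against which to judge it.

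**Conclusion.** The point holds as an error of statement. With d = 0.62, two-sided α = 0.05 and 80% power, the requirement is 42 per group against the 64 printed, a difference of 22 per group or a factor of 1.52. The figure 64 belongs to d = 0.50, and the β of 0.8 should read power = 0.80 (β = 0.20).

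The error leans to the safe side and does not call the recruitment target into question. This assumes a two-sample comparison of means with equal groups and independent observations, which is the only calculation that the stated inputs describe. Which of effect size, power or an unreported inflation factor needs correcting is for the sponsor to say.

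**What to change.** Keep 140 and restate the paragraph so that its figures agree, with power and β labelled correctly. Use whichever of these is true:

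- (a) d = 0.50, two-sided α = 0.05, power 0.80 (β = 0.20), 64 per group.
- (b) d = 0.62, two-sided α = 0.05, about 94% power at 64 per group.
- (c) d = 0.62, two-sided α = 0.05, power 0.80 (β = 0.20), 42 per group, multiplied by a stated inflation factor of about 1.52 to reach 64, with its reason, if one was used.

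The cost is the correction of one paragraph. Enrolment and analysis stay as they are.

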### Randomization

After the baseline assessment, dyads will be randomly allocated to either the intervention or comparison group. Stratified-block randomization will be conducted according to the prefecture in which they live.

### Intervention

#### Intervention group

The intervention comprises a group-based training program on Cognitive Behavior Therapy (CBT)-based resilience-enhancement skills. It is structured across four sessions, with each session lasting 120 min. These sessions will be provided biweekly, considering the busy schedules of mothers. The first author, a qualified and experienced teacher of stress and emotion management as well as parenting, will facilitate the sessions. Each group will consist of 6–14 mothers, and they will receive homework assignments to apply their new knowledge to their daily lives and to share the content of the session with their partners and children at home. At the start of each session, participants will share their experiences with each other, including successes, challenges, and changes in themselves and their family members during the two weeks prior. Partners will not participate in the program.

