#### Control group

Participants in the control group will attend discussion meetings led by a discussion leader, where they will be able to discuss their problems and share how they cope with them. No judgment or criticism will be given. After the two-month follow-up questionnaire, the control group will have the opportunity to participate in the same intervention. Partners will not participate in the discussion meetings.

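### Mothers are randomised individually but treated in interacting groups, and neither the ANCOVA nor the sample size allows for session group; any positive within-group correlation takes the type I error above 5%

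*Protocol article*

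**What the plan says.** The protocol article randomises dyads individually, stratified by prefecture (Randomization), and "The allocation ratio of both groups is 1 to 1" (Methods/design).

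Treatment is then given in groups. For the intervention arm the article states: "Each group will consist of 6–14 mothers" (Intervention group). These mothers exchange experiences at the start of every session, and Session 4 adds exercises in pairs and further sharing. One facilitator runs all intervention sessions. For the control arm: "Participants in the control group will attend discussion meetings led by a discussion leader" (Control group). The abstract describes these as group discussions. No size is given for them, and the article does not say whether membership stays fixed.

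On analysis: "The primary and secondary outcome measures will be analyzed at post-intervention and two-month follow-up using analysis of covariance" (Statistical analysis). The only stated covariate adjustment is for imbalance at baseline. The Sample size calculation section takes a standardised difference of 0.62, a two-sided alpha of 0.05 and power of 0.80 as its only inputs, and concludes that "64 dyads in each group are needed". The recruitment target is 140. Clustering, ICC and design effect are not mentioned anywhere.

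**The concern.** Mothers who go through the same sessions together influence one another. Discussion dynamics, a dominant member or an unusually cohesive group can move several outcomes in the same direction. Individual randomisation does not remove this, because the correlation arises after allocation, through delivery.

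An ANCOVA that treats mothers as independent puts variation between groups down to individual variation and so overstates the information in the data. Seventy intervention mothers form only about 5 to 12 groups (70/14 = 5; 70/6 = 11.7), so chance differences between a few groups could be read as a programme effect. The named model serves the primary and all secondary outcomes, and the error runs towards false positive findings.

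**Working it through.** **Inputs from the article.** d = 0.62; two-sided alpha 0.05; power 0.80 (printed as β = 0.8 and read here as power); 64 per arm needed; 140 recruited at 1:1, so 70 per arm; intervention groups of 6–14.

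**Assumptions, not in the article.** Mean group size m = 10 (the midpoint of 6–14), also applied to controls in the two-arm case; ICC of 0.02, 0.05 or 0.10, with 0.01 as a low value.

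**Step 1: the plan's own figure.** A two-sample t-test with d = 0.62, alpha 0.05 two-sided and power 0.80 needs 42 per arm (41 by the normal approximation), not 64. With 64 per arm the power at d = 0.62 is 94%. The figure of 64 is what d = 0.50 gives (63.8, rounded up). That mismatch is a separate matter, but it means the planning effect is unclear, so power is shown for both values.

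**Step 2: variance inflation.** DE = 1 + (m − 1) × ICC. With m = 10:
- ICC 0.02: 1 + 9 × 0.02 = 1.18
- ICC 0.05: 1 + 9 × 0.05 = 1.45
- ICC 0.10: 1 + 9 × 0.10 = 1.90

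The variance of the treatment difference is multiplied by V = DE if both arms cluster, and by V = (1 + DE)/2 if only one does (1.09, 1.225, 1.45).

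**Step 3: type I error when groups are ignored.** Alpha = 2[1 − Φ(1.96/√V)].

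| ICC | Both arms, formula | Both arms, simulated | One arm, formula | One arm, simulated |
|---|---|---|---|---|
| 0.01 | 6.0% | 5.9% | 5.5% | 5.4% |
| 0.02 | 7.1% | 7.1% | 6.0% | 6.1% |
| 0.05 | 10.4% | 10.6% | 7.7% | 7.8% |
| 0.10 | 15.5% | 15.3% | 10.4% | 10.5% |

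The simulation used a baseline-adjusted ANCOVA with 7 groups of 10 per arm, an assumed baseline correlation of 0.5 and 20,000 runs. Adjusting for baseline does not remove the inflation. Over m = 6 to 14 and ICC 0.01 to 0.10, with both arms clustered, the formula gives 5.6% to 19.6%.

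**Step 4: power when clustering is allowed for.** Effective n per arm = 64/V, entered in the two-sample t-test. With both arms clustered this is 64/1.18 = 54, 64/1.45 = 44 and 64/1.90 = 34.

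| ICC | d = 0.62, both arms | d = 0.62, one arm | d = 0.50, both arms |
|---|---|---|---|
| none | 94% | 94% | 80% |
| 0.02 | 89% | 91% | 73% |
| 0.05 | 82% | 88% | 64% |
| 0.10 | 71% | 82% | 52% |

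**Step 5: when is 80% lost at d = 0.62?** The tolerable inflation is 64/41.82 = 1.53. With both arms clustered, ICC = 0.53/(m − 1), which is about 0.106 at m = 6, 0.059 at m = 10 and 0.041 at m = 14.

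The figures in Steps 4 and 5 leave out two things that pull in opposite directions: the gain from baseline adjustment, and the smaller degrees of freedom of a test that rests on a limited number of groups.

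**The case against.** The other side has four arguments.

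1. **Power.** A reader might infer that the stated 80% power fails. The article does not support that. At its own d = 0.62 the design has 94% before clustering and, with groups of 10 in both arms, stays above 80% at ICC 0.02 and 0.05. A shortfall at every ICC shown appears only at d = 0.50, which the article never states. This argument stands.

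2. **Control arm.** A reader might infer that both arms are treated in small groups. The 6–14 range is given for the intervention arm only. If only that arm clusters, the excess over 5% is roughly half as large. This stands, and it is why both cases are shown.

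3. **The ICC is unknown.** The inflation depends on a positive ICC that the article does not give, and at 0.01 the error is only about 6%. Having one facilitator removes facilitator differences within the intervention arm. This stands as to size. It does not remove correlation that arises from the mothers' interaction, which the programme deliberately encourages.

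4. **Level of detail.** A journal article is brief, and a statistical analysis plan could add a group term. That is possible. But the article names a model for every outcome and reports a finished sample size, and neither has a place for session group. A plan that added one would be changing what is written here, so this argument stands only in part.

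**Conclusion.** The point holds in a conditional form. Treatment is delivered in interacting groups, and the named ANCOVA and the sample size treat mothers as independent. For any positive within-group correlation the ANCOVA's standard errors are too small and its type I error is above 5%. Under the assumed group size and ICCs of 0.02 to 0.10, the error is about 7% to 16% with both arms clustered and about 6% to 10% with only the intervention arm clustered.

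How large the problem is in this trial cannot be known from the article, because it gives neither an ICC nor a control group size. Loss of the stated power is possible but not demonstrated: at d = 0.62 and m = 10 it needs an ICC above about 0.06 in both arms. The point is worth correcting before analysis because it bears on the primary test and costs little.

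**What to change.** - Record a session-group identifier for every mother in both arms. This is easy during the trial and may be hard to reconstruct afterwards.
- Replace the ANCOVA for the mothers' outcomes with a linear mixed model containing arm, baseline score and a random session-group effect. Let the group variance differ by arm, or use a partially nested form if control groups do not have stable membership. Use Kenward-Roger or Satterthwaite degrees of freedom.
- Describe how control discussion groups are formed and how large they are.
- State power over a range of ICCs, with the planning effect made explicit. Leave enrolment unchanged.

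The cost is one data field and revised analysis wording. Confidence intervals will be wider: with both arms clustered at m = 10, by a factor of about √1.18 = 1.09, √1.45 = 1.20 or √1.90 = 1.38 at the three assumed ICCs. The group variance will be estimated imprecisely from about 5 to 12 intervention groups, and the stated power will look less favourable.
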